### Randomisation and allocation concealment

Participants will be allocated into either the treatment or control group using randomisation with computerised block minimisation to stratify for severity based on baseline ONLS score (mild ≤ 3, moderate/severe ≥ 4) and recruitment site to ensure even distribution between groups. Participants will also be stratified by IVIg treatment (yes/no) to minimise the likelihood that small numbers of participants receiving this expensive therapy may skew the cost-effectiveness analysis if not controlled for across the groups. Randomisation will be conducted by the King’s College London Clinical Trials Unit to ensure both the validity and balance of the randomisation and support the successful blinding of the outcome assessor for the intervention duration. Once allocation has taken place, the outcome observer will receive a blinded email confirming the participant number, and the research physiotherapist will receive an un-blinded email confirming participant number and allocation. In order to maintain observer blindness throughout the study period, participants will be requested not to discuss the intervention with the outcome assessor.

### Interventions

#### Control group

Participants allocated to the control group will receive by post a letter advising them that they have been allocated to the information and advice group and including the UK Physical Activity Guidelines factsheet outlining the benefits of regular exercise and the recommended level of exercise for adults or older adults [36] and a copy of the Physical Activity Readiness Questionnaire (PAR-Q) [37]. This group will not receive any contact with the study physiotherapist. They will receive any other usual medical care which may include pharmacological, physical or other therapy interventions deemed necessary by their doctor during the study period. Participants will be requested to try and avoid having additional physiotherapy for their IN during the study but treatment not directly related to their IN will not be restricted.

All referrals to other therapies and the specific interventions applied will be meticulously documented in both groups using the Client Service Receipt Inventory (CSRI) [38]. Data will include service utilisation in the preceding month (home-help, personal and informal care etc.) and less regularly used services in the preceding twelve months (General Practitioner (GP) visits, hospital admission etc.). Informal care and financial costs borne by carers will also be estimated and recorded.

#### Intervention group

In addition to usual care (as characterised above) the intervention group will be prescribed tHEP by the study physiotherapist. Participants will undergo a clinical interview and objective evaluation of their symptoms, activity limitations and any underlying impairments likely to affect their ability to exercise. In addition, in order to foster uptake and adherence to exercise behaviour, the therapist will ask participants to identify their preferences for exercise type and location and any factors that they feel may affect their willingness or ability to carry out a tHEP and how these may be overcome. This information will be used to facilitate the development of individualised exercise programmes tailored to take account of participants SoC and personal beliefs and that include physical activity and exercise goals identified by participants. Based on this assessment, the physiotherapist will prescribe a tailored progressive programme of aerobic and three strengthening exercises. Demonstration and practice of each exercise will ensure participants are carrying them out effectively, safely and with the confidence to continue exercising alone. Participants will be asked to continue the programme by themselves at home for twelve weeks. The therapist will advise participants on how and when to progress their exercises and this will be reinforced in follow-up telephone calls.

Aerobic exercise prescription will be informed by previous neurological exercise interventions [23, 24], evidence based exercise guidelines [39, 40] and participant preference. The dosage of exercise prescribed will be based on the recommendations of the UK Activity Guidelines [36]. Thus participants will be encouraged to gradually build up to at least the minimum recommended guideline amount of 150 min of moderate exercise a week. Moderate intensity exercise such as brisk walking or cycling should make adults feel as if they are breathing harder and their heart is beating faster but that they are still able to carry on a conversation. Participants will be taught how to use the Category Ratio 10 scale (CR-10) for rating of perceived exertion (RPE) [41] to evaluate exercise intensity where moderate intensity is graded at CR-10 grade 4.

Participants already meeting the guidelines at a moderate level, or those participants who build up to this level during the intervention period will be encouraged to set goals to either increase the exercise duration or to increase the intensity of exercise to a vigorous level [42]. Vigorous intensity exercise such as running or sporting activity, will make adults feel they are breathing much harder, their hearts are beating rapidly and they will find it more difficult to carry on a conversation. This intensity of exercise is graded 7 on the CR-10 of RPE [41].

Each participant will also be prescribed three strengthening exercises that target weak muscles, chosen from a standardised menu of strengthening exercises compiled by the study physiotherapist and informed by the literature and evidence based exercise guidelines [24, 40, 43, 44]. Each exercise, and any modifications or progressions, is facilitated by an exercise sheet supplied to the participant, with written and pictorial instructions based on those available on the peer reviewed website www.physiotherapyexercises.com [45]. In order to standardise exercise intensity participants will be advised to perform strengthening exercises at a RPE of 7–10 on the CR-10 [41, 46] with the goal of achieving 3 sets of 8–10 repetitions of each exercise prior to progression. Altering starting position may be used to eliminate or increase the influence of gravity on muscle activity and adding external resistance such as weighted bands or elastic resistance bands, may be used to increase the intensity of exercise as required. Examples of exercises include: heel raises in standing, squats and knee extension in sitting using weighted ankle bands.

Participants in the treatment group will receive a minimum of three follow-up telephone calls from the physiotherapist during the twelve week intervention period. The physiotherapist will use the calls to encourage and monitor adherence, discuss any adaptations or progressions to exercises and to review goals [47]. Participants will be asked to complete a daily exercise diary to monitor their adherence to the programme and to record any adverse events or barriers to exercise they encounter.

#### Adverse event reporting

Participants in both groups will be asked to contact either the principal investigator or research physiotherapist if they experience any adverse events during the study/intervention period. All events will be recorded and reviewed by the principal investigator and the participant’s GP informed if appropriate. Serious adverse events will be referred to the study sponsor and a monitoring group will be convened in order to review the event and ongoing trial safety. Adverse events will be included as a secondary outcome of the study.

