#### Secondary outcome measures

All of the following secondary outcome measures will be assessed at baseline, twelve weeks and twelve months:

*Activity limitation* will also be assessed as a secondary outcome using the Overall Neuropathy Limitations Scale (ONLS) [34]. This is a 12 item ordinal scale of activity limitation developed from the ODSS, which was used to calculate sample size for the present study [35].

*Fatigue* will be assessed using the Rasch-modified Fatigue Severity Scale (RFSS) [50]. This seven-item scale is a Rasch-built modified version of the Fatigue Severity Scale, and was developed specifically to address fatigue in individuals with immune-mediated neuropathy. The authors report good psychometric properties for the scale.

*Psychological wellbeing* will be assessed using the Hospital Anxiety and Depression Scale (HADS) [51]. The scale consists of separate anxiety and depression subscales of seven items each and has been found to correlate well with other measures of depression and anxiety.

*Functional health and well being* will be assessed using the Medical Outcomes Short Form 12 (SF-12). The norms-based scoring system allows direct data comparisons to be made between the SF-12 and other generic health surveys [52, 53].

*Levels of physical activity* will be assessed using the 7-question International Physical Activity Questionnaire (IPAQ-short). The questions ask participants to report the frequency and duration of moderate activity, vigorous activity and walking, and to rate the proportion of time they spent sedentary in the previous week. The scale has shown acceptable measurement properties, similar to other self-report assessments [54].

*Health beliefs* will be assessed using the Brief Illness Perceptions Questionnaire (Brief-IPQ) [55] developed from the revised Illness Perceptions Questionnaire (IPQ-R) [56]. Nine questions address participants beliefs with regard to various features such as perceived severity of consequences, perceived chronicity of an illness or condition, and perceived control over the course or treatment of a given condition. Participants respond on an eleven point Likert scale (for example, 0 = no symptoms at all, 10 = many severe symptoms).

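### During the 12-week programme only the exercise arm has a prompted record of adverse events, so a pooled comparison of non-serious events would be biased against exercise

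*Protocol article*

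**What the plan says.** Four parts of the protocol article bear on this.

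- **Status.** Under Adverse event reporting: "Adverse events will be included as a secondary outcome of the study".
- **Route common to both arms.** The same section states: "Participants in both groups will be asked to contact either the principal investigator or research physiotherapist if they experience any adverse events". Events are then recorded and reviewed centrally, and serious ones go to the sponsor. No separation by source is mentioned.
- **Additional route in the exercise arm.** Under Intervention group, participants are to "complete a daily exercise diary to monitor their adherence to the programme and to record any adverse events". That arm also has a face-to-face assessment and telephone follow-up: "Participants in the treatment group will receive a minimum of three follow-up telephone calls from the physiotherapist during the twelve week intervention period".
- **Control arm.** Under Control group, participants are posted a letter, a factsheet and a readiness questionnaire, and "This group will not receive any contact with the study physiotherapist".

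The Secondary outcome measures section opens with "All of the following secondary outcome measures will be assessed at baseline, twelve weeks and twelve months" and then names its instruments. None of them is an adverse event item. The service-use inventory is completed in both arms and covers GP visits and hospital admissions, but it records use of services, not adverse events.

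**The concern.** An outcome compared between randomised arms has to be looked for in the same way in both. Here one arm is asked every day for 12 weeks to write down adverse events. The other has to recognise an event, decide that it matters and get in touch unprompted. Minor and moderate events, such as soreness, a strain or a passing increase in fatigue, are the ones most likely to be written in a diary and least likely to prompt a call.

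If all reports are pooled, an excess in the exercise arm could be real harm, fuller recording, or both, and the data would not separate them. The article presents the programme as a possible standard of care, so the size of any non-serious harm is something that readers will want from the trial.

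There is also an inconsistency. The Control group section rules out contact with the study physiotherapist, while Adverse event reporting names that physiotherapist as one of two people whom controls may contact. The two sections must be reconciled.

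**Working it through.** The article gives no adverse event rate and no capture rate, so there is no plan figure to reproduce. The text fixes the direction of the bias; the arithmetic only shows how its size depends on assumptions.

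**Step 1. Stated routes side by side**

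| Route | Exercise arm | Control arm |
|---|---|---|
| Participant makes contact | Yes | Yes |
| Daily diary asking for adverse events | Yes, during the programme | None described |
| Physiotherapist calls | At least three in 12 weeks; adverse events not among their stated purposes | None |
| Adverse event item among the listed scheduled measures | None listed | None listed |
| Service-use inventory (GP visits, admissions) | Yes | Yes |

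The asymmetry is the diary. The calls are a further chance to mention an event.

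**Step 2. Size during the programme**

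Let *p* be the true proportion with at least one event, equal in both arms, and let *c1* and *c0* be the probabilities that such a participant is recorded as having one in the exercise and control arms. The observed proportions are *p* × *c1* and *p* × *c0*, so the false risk ratio is *c1*/*c0*; *p* cancels. All capture values below are assumptions.

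| *c1* | *c0* | False risk ratio |
|---|---|---|
| 0.90 | 0.70 | 0.90/0.70 = 1.29 |
| 0.90 | 0.60 | 0.90/0.60 = 1.50 |
| 0.90 | 0.50 | 0.90/0.50 = 1.80 |
| 0.90 | 0.40 | 0.90/0.40 = 2.25 |
| 0.70 | 0.50 | 0.70/0.50 = 1.40 |
| 0.70 | 0.70 | 0.70/0.70 = 1.00 |

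**Step 3. What that means at this sample size**

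The Sample size section recruits 70 people; equal allocation gives 35 per arm. Take *p* = 0.4 and ignore attrition.

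- Capture 90% against 50%: expected counts are 35 × 0.4 × 0.9 = 12.6 and 35 × 0.4 × 0.5 = 7.0, a false risk difference of 0.36 − 0.20 = 0.16. Fisher's exact test at 5% two-sided rejects in 24% of trials.
- Capture 90% against 70%: expected counts are 12.6 and 9.8, and the test rejects in 7%.
- Capture 90% in both arms: expected counts are 12.6 and 12.6, and the test rejects in 3%.

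Over true risks of 0.2 to 0.6, rejection is 9 to 43% when control capture is 50%, 4 to 11% when it is 70%, and 2 to 3% when capture is equal.

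**Step 4. Dilution over the full follow-up**

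No diary is described after the programme. Suppose that capture is then *c0* in both arms and that a share *w* of true events falls within the 12 weeks. The false ratio of event counts over the whole period is *w* × (*c1*/*c0*) + (1 − *w*). If events occur at a constant rate over 52 weeks, *w* = 12/52 = 0.23. Capture of 90% against 40% then gives 0.23 × 2.25 + 0.77 = 1.29, and 90% against 70% gives 0.23 × 1.29 + 0.77 = 1.07. If events cluster within the programme, *w* rises and the ratio moves back towards the values in step 2.

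**The case against.** Several objections have force.

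- **The calls.** A reader might infer that events are actively sought by telephone. The article does not say so: "The physiotherapist will use the calls to encourage and monitor adherence, discuss any adaptations or progressions to exercises and to review goals". This stands, and the point rests on the diary alone.
- **A condensed article.** The full protocol and the case report forms may contain an adverse event question for both arms. That is possible, and the absence of an item from the listed measures does not prove otherwise. But the article does more than stay silent: it states one route for both arms and adds a prompted one for a single arm.
- **No comparison is specified.** The analysis section gives no contrast or test for adverse events, and the reporting may be descriptive. This stands in part. Yet a secondary outcome of a two-arm trial will be read by arm, and a descriptive table carries the same bias.
- **The safety data as a whole.** A reader might infer that the safety comparison is uninterpretable. The documents do not support that. Serious events follow the same stated route in both arms, the service-use inventory gives a symmetric view of GP visits and admissions, and the diary is tied to 12 weeks. Because the bias runs against exercise, a result showing no excess would still be informative.
- **The physiotherapist as contact.** A reader might infer that controls are prevented from reporting. They are not, since the principal investigator is offered as the alternative. What remains is wording that needs reconciling.
- **The size.** The ratios follow entirely from the assumed capture rates. This stands; they are illustrations, not estimates.

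**Conclusion.** The point holds in a limited form. As written, the plan gives unequal ascertainment of non-serious adverse events during the 12-week programme, because one arm has a prompted daily record and the other is described as having only self-initiated contact. A between-arm comparison that pools all sources is biased against exercise, and analysis cannot repair it afterwards.

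The size is unknown. It equals the ratio of capture probabilities within the programme, 1.29 to 2.25 under an assumed 90% against 70 to 40%, and it is smaller over the full follow-up if events are spread evenly. These values assume equal true risk and better capture with a diary than without one. The primary outcome is untouched, and serious events are little affected. The problem is worth correcting because adverse events are a declared outcome and the correction is cheap.

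**What to change.** Add one identical, neutrally worded question to the existing 12-week and 12-month questionnaires in both arms. It should ask about any new or worsened health problem since the last assessment, its type and its seriousness, without referring to exercise. Then:

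- have the answers received and handled by someone other than the blinded outcome assessor, since a description of an event could reveal the allocation;
- base the between-arm comparison of non-serious events on this question;
- report serious events from all sources in both arms;
- list diary and spontaneous reports descriptively, by source;
- reconcile the Control group section with Adverse event reporting on whether controls may contact the study physiotherapist.

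The cost is one item on each of two questionnaires already planned, with no new visit. There are two downsides. Answers will carry recall error over 12 weeks and then over the months to the final assessment, and this may be smaller in the exercise arm because keeping a diary can aid memory, so the comparison will be fairer but not perfectly balanced. Answers will also be missing for participants who do not return a questionnaire; the Sample size section allows for 25% attrition at twelve months.

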### Outcome assessment

#### Primary outcome

*Activity limitation* will be assessed using the recently validated Rasch based Overall Disability Scale (RODS) [48]. This 24-item interval scale for activity limitation has greater responsiveness than previous ordinal measures [49]. Scores for the RODS will be collected at baseline, at the end of the twelve week intervention period and at a twelve month follow up.

#### Secondary outcome measures

All of the following secondary outcome measures will be assessed at baseline, twelve weeks and twelve months:

*Activity limitation* will also be assessed as a secondary outcome using the Overall Neuropathy Limitations Scale (ONLS) [34]. This is a 12 item ordinal scale of activity limitation developed from the ODSS, which was used to calculate sample size for the present study [35].

*Fatigue* will be assessed using the Rasch-modified Fatigue Severity Scale (RFSS) [50]. This seven-item scale is a Rasch-built modified version of the Fatigue Severity Scale, and was developed specifically to address fatigue in individuals with immune-mediated neuropathy. The authors report good psychometric properties for the scale.

*Psychological wellbeing* will be assessed using the Hospital Anxiety and Depression Scale (HADS) [51]. The scale consists of separate anxiety and depression subscales of seven items each and has been found to correlate well with other measures of depression and anxiety.

*Functional health and well being* will be assessed using the Medical Outcomes Short Form 12 (SF-12). The norms-based scoring system allows direct data comparisons to be made between the SF-12 and other generic health surveys [52, 53].

*Levels of physical activity* will be assessed using the 7-question International Physical Activity Questionnaire (IPAQ-short). The questions ask participants to report the frequency and duration of moderate activity, vigorous activity and walking, and to rate the proportion of time they spent sedentary in the previous week. The scale has shown acceptable measurement properties, similar to other self-report assessments [54].

*Health beliefs* will be assessed using the Brief Illness Perceptions Questionnaire (Brief-IPQ) [55] developed from the revised Illness Perceptions Questionnaire (IPQ-R) [56]. Nine questions address participants beliefs with regard to various features such as perceived severity of consequences, perceived chronicity of an illness or condition, and perceived control over the course or treatment of a given condition. Participants respond on an eleven point Likert scale (for example, 0 = no symptoms at all, 10 = many severe symptoms).

*Self-efficacy;* an individuals confidence in their ability to exercise, will be measured using the self-efficacy for exercise (SEE) scale [57]. The scale examines 9 potential barriers to exercise, such as feeling tired or depressed; participants are asked to rate each item on an eleven point Likert scale spanning the extent to which they feel confident that they could exercise in the presence of a particular barrier (0 = Not confident, 10 = Very confident). The authors report good internal consistency (alpha 0.92) and good predictive validity for the scale [57].

*Adherence* to the tailored home exercise programme in the study will be evaluated using a) the Exercise Adherence Rating Scale (EARS) and b) self-report diary entries.The EARS has been developed based on the Medication Adherence Rating Scale [58] and evaluates barriers to adherence for prescribed exercise by asking participants to rate, on a five-point Likert scale, the extent to which they agree with sixteen statements about their exercise adherence (for example, “I forget to do my exercises”, “I’m not sure how to do my exercises”). The EARS will only be completed by participants randomised to the tHEP intervention.Self-report exercise diaries record exercise type, completion and factors affecting exercise. The number of repetitions of strengthening exercise and duration of aerobic exercise will be used to calculate overall adherence as a proportion of the exercise prescribed.

### Cost-effectiveness and cost-utility analyses

In order to evaluate the cost-effectiveness and cost-utility of the intervention in relation to advice and usual care, participants in both groups will complete the Client Services Receipt Inventory (CSRI) and the EQ-5D at baseline and twelve month follow-up.

The CSRI is a scale developed for collecting data relating to service use and has been used in a large number of evaluations of health and social care interventions over the past 30 years [38]. The questionnaire records the interviewee’s use of health and social care services, accommodation and living situation, income, employment and benefits. Service use data are combined with appropriate unit costs [59] to generate total care costs per patient. Lost employment will be valued using average wage rates.

The EQ-5D [60] is a brief scale designed to measure health related quality of life across five dimensions: mobility, self-care, usual activities, pain/discomfort and anxiety/depression. For each domain participants are asked to rate their current health using a five point scale to describe the extent to which they can perform activities (“No problems” to “Unable to perform”). The scale also includes a visual analogue scale on which participants mark their current health status between 0 (worst health they can imagine) and 100 (best health they can imagine). Quality Adjusted Life Years (QALYs) will be derived from the EQ-5D scores for the cost-utility analysis.

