**Methods/Design:**

The current study is a pragmatic, prospective, parallel observer-blind, randomised controlled trial to evaluate the efficacy and cost-effectiveness of a twelve week tailored home exercise programme versus advice and usual care. Seventy adults with stable immune mediated inflammatory neuropathy IN will be recruited to the study from two main sources: patients attending selected specialist peripheral nerve clinics in the South East and West Midlands of England and people with who access the GAIN charity website or newsletter. Participants will be randomised to receive either advice about exercise and usual care or a 12 week tailored home exercise programme.

The primary outcome of activity limitation and secondary outcomes of fatigue, quality of life, self-efficacy, illness beliefs, mood and physical activity will be assessed via self-report questionnaire at baseline, 12 weeks and 12 months post intervention. Cost effectiveness and cost utility will be assessed via interview at baseline and 12 months post intervention.

Intention to treat analysis will be our primary model for efficacy analysis. Semi-structured interviews will be conducted with a selected sample of participants in order to explore the acceptability of the intervention and factors affecting adherence to the exercise programme.

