#### Cost-effectiveness and cost-utility analyses

Costs generated from the CSRI will be added to costs of the intervention. These will be derived from information on staff time involved in delivering the intervention and other non-staff costs. The endpoint for the economic analysis will be twelve months when, if costs are lower in the exercise group and outcome better, then the exercise intervention will have been cost-effective. However, if costs are higher and outcomes better then we will construct cost-effectiveness acceptability curves to show the probability that the intervention is cost-effective for different values placed on a change in outcome. Cost-utility analyses will be conducted in a similar way, but will use QALYs as the outcome measure. Uncertainty around the results will be explored using cost-effectiveness planes and acceptability curves.

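### The EQ-5D, the only source of QALYs, is not taken at the existing 12-week assessment, so the QALY difference rests on month 12 alone; on costs, only the one-month-recall items share this gap

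*Protocol article*

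**What the plan says.** All references are to the protocol article.

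- **Collection times.** The Methods section *Cost-effectiveness and cost-utility analyses* says that "participants in both groups will complete the Client Services Receipt Inventory (CSRI) and the EQ-5D at baseline and twelve month follow-up".
- **Source of QALYs.** The same section says "Quality Adjusted Life Years (QALYs) will be derived from the EQ-5D scores for the cost-utility analysis". No other utility source is named.
- **Assessments available.** *Design* has assessments at baseline, at the end of the 12-week intervention and at twelve months. *Primary outcome* and *Secondary outcome measures* take the RODS and the listed questionnaires, among them the SF-12, at all three. The EQ-5D is not in that list.
- **Recall windows of the CSRI.** *Control group* gives two. Care that is used routinely is asked about for one month only: "Data will include service utilisation in the preceding month (home-help, personal and informal care etc". For services used now and then the window is a full year, worded there as "less regularly used services in the preceding twelve months (General Practitioner (GP) visits, hospital admission etc".
- **Intervention cost.** Under *Data analysis*, "Costs generated from the CSRI will be added to costs of the intervention". The article takes that delivery cost from trial records and not from participants' recall, since it is "derived from information on staff time involved in delivering the intervention and other non-staff costs".
- **Horizon.** Also under *Data analysis*: "The endpoint for the economic analysis will be twelve months". The abstract words it differently: "Cost effectiveness and cost utility will be assessed via interview at baseline and 12 months post intervention".

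**The concern.** Supervision, telephone calls and prescribed exercise all fall in the first 12 weeks. If the programme changes utility, the end of that period is an obvious time to look, and the trial already assesses participants then. The one instrument that feeds the QALYs is left out. An analysis plan can choose how to interpolate, but it cannot recover a utility that was never collected.

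Cost-effectiveness and cost utility are the first of the secondary research questions, and randomisation is stratified by IVIg to protect that analysis. A QALY difference that ignores utility at 12 weeks could make the programme look worse or better value than it is, depending on the time course. A narrower version of the same gap affects home-help, personal and informal care, which are asked about only for the month before each assessment. The *Background* says many people with inflammatory neuropathy need long-term informal care, so this cost item may not be small.

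**Working it through.** The article states no QALY or cost figure, so there is none to reproduce. The check asks what two time points can and cannot show.

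**Inputs from the article:** EQ-5D at weeks 0 and 52; an existing assessment at week 12; a 12-month horizon; CSRI recall of one month (regular care) and twelve months (less regular services).

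**Assumptions, not in the article:** QALYs by the trapezoid rule; no between-arm utility difference at baseline; a utility difference of d12 at week 12 and d52 at week 52. Illustrative d12 = 0.05, range 0.03 to 0.08.

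**QALY difference**

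- Two points: ½ × d52.
- Three points: ½ × d12 × (12/52) + ½ × (d12 + d52) × (40/52) = 0.5 × d12 + (40/104) × d52.
- Three points minus two points: 0.5 × [d12 − (12/52) × d52].

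With d12 = 0.05:

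| Gain kept at 12 months | d52 | Two points | Three points | Missed | Share missed |
|---|---|---|---|---|---|
| None | 0 | 0 | 0.0250 | 0.0250 | 100% |
| Half | 0.025 | 0.0125 | 0.0346 | 0.0221 | 64% |
| All | 0.05 | 0.0250 | 0.0442 | 0.0192 | 43% |

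The shares do not depend on d12, because it cancels. Over d12 = 0.03 to 0.08, the QALYs missed run from 0.0115 (d12 = 0.03, all kept) to 0.040 (d12 = 0.08, none kept).

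**Direction.** The two estimates agree when d12 = (12/52) × d52, that is when the 12-week gain is 23% of the 12-month gain (a straight-line course). Below that, two points overstate. For example, with d12 = 0 and d52 = 0.05, two points give 0.0250 and three give (40/104) × 0.05 = 0.0192.

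**Regular care (one-month recall).** The follow-up window covers 1/12 = 8% of the year and none of weeks 0 to 12, which are 12/52 = 23% of it. Let the weekly cost difference be c in weeks 0 to 12 and r × c afterwards. The true total is 12c + 40rc. Scaling month 12 to the year (assumed) gives 52rc, so 12(1 − r)c is missed:

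- r = 0: 12c missed (12c true, 0 estimated)
- r = 0.5: 6c missed (32c true, 26c estimated)
- r = 1: nothing missed

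**Other costs.** A twelve-month recall at month 12 covers weeks 0 to 52, so less regular services in the intervention period are captured. Delivery costs come from staff time and non-staff data and do not depend on participant recall.

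**Timing.** Read literally, the abstract puts the final economic assessment at week 12 + 52 = 64. A twelve-month recall would then reach back only to week 64 − 52 = 12. *Design* and both economic sections say twelve months.

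**The case against.** **The schedule matches the chosen endpoint.** The main efficacy regression uses change to twelve months, the economic endpoint is also twelve months, and fewer questionnaires reduce burden in a 70-person trial. This explains the choice, but a QALY is accumulated over the year, not read off at its end. The cost-effectiveness analysis on the clinical outcome does not need the EQ-5D; the cost-utility analysis does.

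**Direction and size are assumed.** This stands. A reader might infer that the result must be biased against the home exercise programme. The article does not support that: participants build up gradually, so a slow-onset course cannot be excluded, and two points can then overstate the gain. Interpolation and annualisation rules may also properly sit in the full plan.

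**The cost totals are largely covered.** This also stands. A reader might infer that costs as a whole miss the intervention period. They do not: the twelve-month recall reaches baseline on the Methods' timing, and delivery cost is added separately. Only the one-month items are unobserved in weeks 0 to 12, and even for these there is a baseline snapshot as well as the one at month 12.

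**The abstract's wording is loose.** A reader might infer from it that the twelve-month recall fails too. Taken literally, its list of assessment times would also move the 12-week assessment, which *Design* places at the end of the intervention. This is an inconsistency to tidy, not evidence that the recall misses the period.

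**Conclusion.** The point holds in limited form. As planned, the QALY difference cannot reflect utility at the end of the intervention, although an assessment takes place then. If a 12-week gain is kept fully, half or not at all, the two-point calculation misses 43%, 64% or 100% of the three-point QALY gain; if the 12-week gain is under 23% of the 12-month gain, it is too high. These shares rest on the trapezoid rule and equal baseline utility; the absolute QALY figures also rest on an assumed utility gain. The three-point figure is itself an approximation to the true course.

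On costs, the gap is confined to home-help, personal and informal care. The primary efficacy result is unaffected. One stated secondary objective is weaker than it needs to be, and the main remedy is cheap.

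**What to change.** 1. **Add the EQ-5D to the existing 12-week questionnaire.** Compute QALYs by area under the curve over baseline, 12 weeks and 12 months, adjusted for baseline utility. The cost is one brief extra scale per participant at an assessment that already takes place. The abstract says economic data come by interview, so keep the mode of completion the same at all three times.
2. **If forms can no longer change,** report a sensitivity QALY from utilities derived from the SF-12, already collected at all three times. This needs no new data, but it does need a mapping step that the article does not plan.
3. **Optional: a short set of regular-care questions at 12 weeks.** This would observe the one-month items near the end of the intervention, at the price of added burden and possibly an extra interview. Lengthening the month-12 recall for routine care instead would trade extrapolation for recall error.
4. **Reconcile the timing.** Bring the abstract's description of the final economic assessment into line with *Design* and the economic sections, so that the twelve-month recall clearly covers the intervention period. This is a wording change only.
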